## Treatment

### Albendazole

The initial treatment course in arms 2-4 will consist of 400mg bid for three weeks. The second course in arm 3 will consist of 400mg bid for three weeks. Subjects in arm 4 who have not achieved <4000 mf/mL after their first course of albendazole will instead be put on a continuous course of 400mg bid. Albendazole will be provided as 400mg tablets. Patients will be specifically and repeatedly advised that albendazole intake shall follow intake of a standard meal as this importantly enhances the bioavailability of albendazole. Note that at the end of the study, any participants in arm 1 who wish to, will be provided with a 3-week course of albendazole (400mg/day), in line with Gabonese national guidelines for MDA in Loa-endemic populations.

### Ivermectin

Ivermectin will be taken as a stat dose of 150 μg/Kg by subjects in arm 4 who have achieved <4000 mf/mL after their first course of albendazole. Ivermectin will be provided as tablets of 3mg.

### Other

Symptomatic treatment may be provided to subjects in all study arms as clinically indicated, e.g. antihistamines for itching or paracetamol for headache and joint pain.

## Laboratory assessments

### Detection & quantification of microfilariaemia

*L. loa* microfilaraemia will be detected and quantified in peripheral venous blood using Giemsa-stained thick smear microscopy and/or the saponin concentration method as appropriate: thick smear microscopy will be performed first for all samples and saponin concentration will in principle only be performed on samples which are negative for microfilaria by thick smear. Thick smear microscopy will be performed using the Lambaréné method, using a fixed volume (10μL) of blood on a fixed slide surface area (1.8 cm^2^) and read at 10x magnification with a known microscopic optical field diameter in order to allow quantification of microfilaraemia per optical field. Unstained, unfixed sediments of 1mL of saponin-lysed whole blood will be observed at 10x magnification in their entirety in order to quantify microfilaraemia. PCR may be performed on samples as an additional detection/quantification tool, if required. Blood for parasite detection/quantification will be taken from remaining material in one or both of the tubes already collected for respectively haematology and biochemistry, see section 6.4.2. Safety parameters (below).

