## Endpoints

### Primary endpoints

1. Primary efficacy endpoint will be the proportion of subjects with *L. loa* microfilarial levels <100 mf/mL at 6 months after the commencement of treatment
2. Co-primary efficacy endpoint will be the proportion of subjects without microscopically detectable microfilariae (assessed on three consecutive days) at any time point during follow up.

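### Any positive 10 µL smear fails the <100 mf/mL primary endpoint, and the 1 mL saponin count that could correct it is planned only for negative smears, so the primary proportion is biased downward.

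*Protocol*

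**What the plan says.** Protocol section 4.3.1 defines the primary efficacy endpoint as the proportion of participants with "microfilarial levels <100 mf/mL at 6 months after the commencement of treatment". The inequality is strict.

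Section 6.4.1 describes how the density is measured:

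- Order: "thick smear microscopy will be performed first for all samples".
- Smear volume: the smear is made "using a fixed volume (10μL) of blood on a fixed slide surface area".
- Second method: "saponin concentration will in principle only be performed on samples which are negative for microfilaria by thick smear".
- Saponin volume: "Unstained, unfixed sediments of 1mL of saponin-lysed whole blood will be observed at 10x magnification in their entirety".
- Third method: "PCR may be performed on samples as an additional detection/quantification tool, if required".

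The V3 entry in the document history describes the same restriction of saponin to smear-negative samples. The protocol mentions no replicate smears, gives no rule for a smear showing one or a few microfilariae, and does not say which method's value decides the endpoint when more than one is available.

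**The concern.** The threshold coincides with the smallest non-zero result the smear can give. One microfilaria in 10 µL reads as 100 mf/mL, which is not below 100. A participant whose true density is under the threshold fails if a single microfilaria falls into the drop.

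The two kinds of smear error are handled differently. A participant above the threshold whose smear happens to be negative goes on to the 1 mL count, which usually shows the true position. A participant below the threshold whose smear happens to be positive is not required to have any further count.

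The trial is meant to pick out regimens for later comparative studies, and the primary proportion may rest on as few as 8 evaluable participants per treatment arm, so one misclassified participant moves an arm by 1/8 = 12.5 percentage points. The loss is greatest for a regimen that leaves people just under the threshold, so it need not be equal across arms.

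**Working it through.** **Inputs.** From section 4.3.1: success means below 100 mf/mL. From section 6.4.1: smear volume 10 µL = 0.01 mL, saponin volume 1 mL, saponin in principle only after a negative smear. From section 5.2: 8 evaluable per treatment arm, one third loss, 6 controls. Assumptions made here: counts are Poisson and the whole 10 µL smear is read.

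**The plan's own figure.** 8 / (1 − 1/3) = 12 per treatment arm, and 6 + 3 × 12 = 42. This reproduces and is not in question. It serves below as the upper limit on the cost. The protocol gives no figure for misclassification.

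**One-count limit.** 1 / 0.01 mL = 100 mf/mL. If only part of the smear is read, one count stands for more than 100 mf/mL, and a positive smear still fails.

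**Formulas.** For a true density d in mf/mL:

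- P(smear positive) = 1 − exp(−d/100)
- P(success, current rule) = exp(−d/100) × P(Poisson(d) ≤ 99)
- P(success, saponin on every sample) = P(Poisson(d) ≤ 99)

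| True density (mf/mL) | Smear positive | Scored success, current rule | Scored success, saponin on all |
|---|---|---|---|
| 0 | 0% | 100% | 100% |
| 10 | 9.5% | 90% | 100% |
| 20 | 18% | 82% | 100% |
| 50 | 39% | 61% | 100% |
| 80 | 55% | 44% | 98% |
| 90 | 59% | 34% | 84% |
| 105 | 65% | 10% | 30% |
| 110 | 67% | 5% | 16% |
| 150 | 78% | about 0% | about 0% |

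At 20 and 50 mf/mL the whole loss comes from the smear. At 90 mf/mL the smear accounts for 59%. Chance counts of 100 or more in the saponin sediment bring the total failure rate to 1 − 0.34 = 66%, and 16% would remain with saponin on every sample.

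**Averages over true successes.** These need a distribution of month-6 densities, which the documents do not give. As illustrations of the smear-positive loss:

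- uniform on 0 to 100 mf/mL: the mean of 1 − exp(−d/100) is exp(−1) = 37%
- log-uniform on 1 to 100 mf/mL: 17%

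**Low-count variant.** Doing saponin only on smears with 5 or fewer microfilariae gives almost the same results as doing it on all: 100% at 50 mf/mL, 98% at 80 and 84% at 90.

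**The case against.** The strongest case against is that the size is unknown. Participants who clear completely are never misclassified, and at 5 to 10 mf/mL the error is only 5% to 10%. The protocol's background cites albendazole reducing levels to 20% of the pre-treatment value at 6 months. On that figure alone, a month-6 density of 20 to 99 mf/mL would need a baseline of about 100 to 495 mf/mL (20/0.2 to 99/0.2). Adding the cited ivermectin reduction of 70–90%, a baseline of 5,000 would end at 5,000 × 0.2 × 0.1 to 0.3 = 100 to 300 mf/mL, a true failure anyway. The cited regimens differ from this trial's, so this is only indicative. Still, a reader might infer that many true successes will be lost, and the documents do not establish that.

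Three other stronger readings are tempting, and the text does not support them:

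- **That a positive smear can never be rechecked.** Section 6.4.1 says in principle, leaves the choice of method open as appropriate, and allows PCR. Saponin on a low-positive smear is not required, but it is not barred.
- **That the error runs in one direction only.** Just above the threshold a small reverse error exists: about 10% of participants at 105 mf/mL are scored as successes. The net bias is still downward.
- **That the primary and co-primary endpoints become the same thing.** That would hold only if the smear were the sole method. A smear-negative participant with 1 to 99 microfilariae in the 1 mL sediment meets the primary endpoint and still has microfilariae seen under the microscope. The co-primary, "the proportion of subjects without microscopically detectable microfilariae (assessed on three consecutive days"), also differs in timing and repetition: it can be met at any point in follow-up.

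It is also fair to say that the trial is a descriptive pilot, that one rule applies to all arms, and that the median reductions among the secondary endpoints would still show a large fall. That limits the harm but does not repair the primary proportion. The statistical analysis plan could say which value decides, but it cannot supply a count that was not made.

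**Conclusion.** The point holds as a net downward bias of unknown overall size in the primary proportion. It follows from three items of the protocol taken together: a strict threshold of 100 mf/mL, a 10 µL smear, and saponin prescribed only after a negative smear. Under Poisson sampling with the whole smear read, a positive smear fails a true success 18%, 39% or 59% of the time at 20, 50 or 90 mf/mL. The two illustrative averages of 17% and 37% show how far the total depends on the month-6 densities. It would be small if most responders clear fully, and larger if many settle between about 20 and 99 mf/mL. The finding does not touch the sample size or the co-primary endpoint. It is a worthwhile and cheap improvement to the measurement rule, not a defect that invalidates the design.

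**What to change.** In section 6.4.1, require at month 6 the 1 mL saponin count on every participant's sample, or at least on every sample whose smear is negative or shows a low count (for example 5 or fewer microfilariae). State there or in section 4.3.1 that the saponin count, where made, decides whether the participant is below 100 mf/mL.

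The cost is at most 42 saponin readings in total at month 6, some of which the current rule already requires for negative smears. The method is already in use. Because the smear result is not known when blood is drawn, 1 mL must already be available from each participant.

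The statistical downside is slightly more false successes just above the threshold: from about 10% to about 30% at 105 mf/mL, and from about 5% to about 16% at 110. By 150 mf/mL both rules score failure almost always.

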### Safety parameters

Laboratory safety parameters to be measured include full blood count (Hb, Ht, RBC parameters, WBCs, leuko diff, Tr) using 1.2-2.7 ml of EDTA blood and if scheduled (e.g. during treatment), or otherwise clinically indicated, a biochemistry panel (CRP, ALAT, ASAT, γGT, bilirubin, creat, electrolytes and glucose, as appropriate) using 2.7 ml of lithium-heparin blood.

## Immunology

Up to 10mL of lithium heparin blood may be drawn at each immunological assessment time-point (see section 6.2 study visits). Assessment of study subjects may include determination of leukocyte differential counts & immunophenotyping by flow cytometry and quantification of circulating cytokines, eotaxins, eosinophilic degranulation proteins and total IgE in plasma by multiplex bead array and/or ELISA. PBMC and 1:5 diluted whole blood stimulation assays may be performed with Loa-specific antigen (crude adult worm lysate and crude microfilarial lysate) and non-specific stimuli (anti-CD3/PHA) at baseline, during and after albendazole/ivermectin treatment and at the end of follow-up. A panel of Th1-, Th2- and Th17-archetype as well as anti-inflammatory cytokines may be measured in PBMC culture supernatant by multiplex bead array and the predominance & activation of individual Th cell-subsets may be determined by flow cytometry. Eosinophil degranulation proteins may be measured in supernatants of whole blood assays and a dedicated flow cytometry panel may be used to assess non-secreted markers of eosinophil activation (e.g. CD69 and MHC-II up-regulation).

# Safety

## Risks

### Anti-filarial treatment

The risk of treatment-associated adverse events in loiasis are largely associated with the drugs DEC and ivermectin and are thought to be due to their rapid killing of high numbers of *L. loa* microfilariae in peripheral blood. Treatment with albendazole has generally not been associated with such adverse reactions. By only providing ivermectin treatment to those subjects who have already achieved a reduction of microfilaraemia to below 4000 mf/mL, the associated risk of treatment is almost negligible. However, close clinical and laboratory follow-up is planned to optimise the management of any unforeseen events. Symptomatic treatment, e.g. antihistamines, paracetamol, etc., will be provided to all subjects as clinically indicated. A clinical trial insurance will be obtained to cover all patients participating in this trial.

### Phlebotomy

The total volume of venous whole blood drawn over the entire trial, over a ±6 month period, will not exceed 500mL (i.e. the standard volume of blood donation). There may be minor bruising, local tenderness or symptoms of pre-syncope associated with venepuncture, which will not be documented as AEs if they occur. In rare cases arteries or nervous tissue may be injured or a punctured vessel may occlude and induce inflammation of the surrounding tissue.

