### Secondary endpoints

1. Primary safety endpoint will be the occurrence of any grade 3 adverse event (AE) or serious adverse event (SAE), from the commencement of each study arm until 6 months thereafter; such events may be related or unrelated to study procedure.
2. Safety & tolerability will additionally be assessed by the occurrence of all (grade 1-2) adverse events at least possibly related to study therapy, from the commencement of each study arm until 6 months thereafter.
3. Proportion of subjects without peripheral microfilaraemia at 6 months follow up
4. Median reduction of *L. loa* MF at each month post start of treatment and at nadir
5. Median time from commencement of treatment to nadir of *L. loa* microfilaraemia

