### Visits following intake of ivermectin

Subjects in arm 4 who achieve <4,000 mf/mL will receive a single dose of ivermectin under observation, followed by daily visits to record AEs during the first week after intake and twice weekly in the second week. Blood will be drawn for laboratory safety parameters (haematology and biochemistry) and quantification of microfilaraemia on the day of treatment (DRT0), DRT+1, DRT+3, DRT+7, DRT10 and DRT+14. Additional blood may be collected for immunology at DRT0, DRT+1 and DRT+14. (*Visit designations are approximate and may vary by ±1 day in the first week after start of treatment and by ±2 days in the week thereafter.*)

If clinically indicated a physical examination and/or additional blood draw(s) for laboratory safety parameters will be performed.

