## Adverse events

An adverse event (AE) is defined as any untoward medical occurrence in a patient or clinical investigation subject administered a pharmaceutical product and which does not necessarily have a causal relationship with this treatment. An adverse event (AE) can therefore be any unfavourable and unintended sign (including an abnormal laboratory finding), symptom, or disease temporally associated with the use of a medicinal (investigational) product, whether or not related to the medicinal (investigational) product.

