## Grading of AEs

All AEs will be assessed for severity by the investigator. Inherent in this assessment is the medical and clinical consideration of all information surrounding the event including any medical intervention required. Each event will be assigned one of the following categories: mild, moderate, severe, or life-threatening. The criteria below may be used for any symptom not included in the grading scale. Any grade 4 (life-threatening) AE must be reported as an SAE.

The CRF for AEs will reflect only the highest severity for continuous days an event occurred.

• Grade 1 (Mild): Does not interfere with routine activities, minimal level of discomfort

• Grade 2 (Moderate): Interferes with routine activities, moderate level of discomfort

• Grade 3 (Severe): Unable to perform routine activities, significant level of discomfort

• Grade 4 (Potentially life-threatening): Hospitalization or ER visit for potentially

life-threatening event

If a subject is evaluated in an emergency room for nonlife threatening illness or symptoms (i.e., visits emergency department on weekend for mild problems because the physician’s office is closed), the information from that visit will be reviewed and severity of the adverse event will be assessed according to the subject’s clinical signs and symptoms.

As defined by the ICH guideline for GCP, the term “severe” is often used to describe intensity (severity) of a specific event (as in mild, moderate, or severe myocardial infarction); the event itself however, may be of relatively minor medical significance (such as severe headache). This is not the same as “serious”, which is based on subject/event outcome or action criteria usually associated with events that pose a threat to a subject’s life or functioning. Seriousness (not severity) serves as a guide for defining regulatory reporting obligations.

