## Assessment of AE relatedness

The investigator must assign a relationship of each AE to the receipt of study medication. The investigator will use clinical judgment in conjunction with the assessment of a plausible biologic mechanism, a temporal relationship between the onset of the event in relation to receipt of the investigational product(s), and identification of possible alternate aetiologies including underlying disease, concurrent illness or concomitant medications. The following guidelines should be used by investigators to assess the relationship of an AE to study medication:

• Not related: No relationship to investigational product. Applies to those events for which evidence exists that there is an alternate aetiology.

• Unlikely: Likely unrelated to the investigational product. Likely to be related to factors other than investigational product, but cannot be ruled out with certainty.

• Possible: An association between the event and the administration of investigational product cannot be ruled out. There is a reasonable temporal association, but there may also be an alternative etiology such as the subject’s clinical status or underlying factors including other therapy.

• Probable: There is a high degree of certainty that a relationship to the investigational product exists. There is a reasonable temporal association, and the event cannot be explained by known characteristics of the subject’s clinical state or factors including other therapy.

• Definite: An association exists between the receipt of investigational product and the event. An association to other factors has been ruled out

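### Section 7.1.2 exempts needle-associated pre-syncope from AE recording without a grade limit, which conflicts with a safety endpoint that counts grade 3 events whether or not the procedure caused them

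*Protocol*

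**What the plan says.** Section 7.1.2 (Phlebotomy) names three expected effects of venepuncture: minor bruising, local tenderness and "symptoms of pre-syncope associated with venepuncture, which will not be documented as AEs if they occur". The word for minor stands before bruising only. Pre-syncope is given no grade ceiling, no time window, and no rule for deciding when it is associated with the needle.

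Section 4.3.2 makes any grade 3 AE or any SAE, from the start of the arm to 6 months, the primary safety endpoint, and states that "such events may be related or unrelated to study procedure". A further safety endpoint is the "occurrence of all (grade 1-2) adverse events at least possibly related to study therapy".

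Section 7.2 defines an AE as an untoward sign, symptom or disease in temporal association with the product, "whether or not related to the medicinal (investigational) product". Section 7.4 defines the relevant grade by function: "Grade 3 (Severe): Unable to perform routine activities, significant level of discomfort". Section 7.5 requires a causality judgement on recorded events: "The investigator must assign a relationship of each AE to the receipt of study medication". Section 7.4 makes every grade 4 event an SAE, and section 7.6 has SAEs recorded in all participants. Section 7.1.2 does not say how its exemption relates to either rule.

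**The concern.** Bruising and tenderness at the puncture site are local and are not readily mistaken for a drug effect. Pre-syncope is systemic. To say that it is associated with venepuncture is to decide its cause, and section 7.5 provides a five-level scale for that decision. Section 7.1.2 lets the decision be made before there is an AE record, by an investigator who knows the allocation (the trial is open-label), and at visits close to dosing. An event exempted in this way gets no grade and no relatedness category, and section 7.3 says that no AEs are solicited, so no symptom checklist would recover it.

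At stake is agreement between what the AE form captures and what the primary safety endpoint says it counts. Safety and tolerability is the first secondary objective, and section 3.2.3 notes that albendazole given ahead of ivermectin or DEC to lower microfilarial load had not yet been examined.

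**Working it through.** **Setting the sections side by side.** Take a participant who nearly faints during a scheduled draw, cannot carry on routine activities, is not hospitalised, and whose episode the investigator puts down to the needle.

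- Section 7.2: an AE, because cause is irrelevant to the definition.
- Section 7.4: grade 3 on the functional criterion.
- Section 4.3.2: counts in the primary safety endpoint, because relation to procedure is irrelevant.
- Section 7.1.2: not documented as an AE.

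The last line cannot be followed together with the first three. If the same episode met an SAE criterion or were grade 4, sections 7.4 and 7.6 would still require it to be recorded. If the investigator did not attribute it to the needle, section 7.1.2 would not apply. The conflict is therefore confined to non-serious events attributed to the draw. It is direct for grade 3 and touches grades 1-2 through the general AE definition.

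**Draws near dosing.** Inputs are the schedules in sections 6.2.1 to 6.2.4 and the arm sizes in section 5.2 (8/(1 - 1/3) = 12 per treatment arm; 6 + 3 x 12 = 42, as stated). Twice monthly is taken as every 14 days to day 182, and re-treatment is assumed to start at week 8. The screening draw is left out.

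- First window, all arms: DT0, +1, +3, +7, +10, +14, +17, +21 = 8 draws.
- Second window, arms 3 and 4: after ivermectin the protocol specifies "quantification of microfilaraemia on the day of treatment (DRT0), DRT+1, DRT+3, DRT+7, DRT10 and DRT+14" = 6 draws, with a similar schedule for albendazole re-treatment.
- Arms 1 and 2: 8 + 5 weekly + 9 twice-monthly = 22 per person.
- Arms 3 and 4: 8 + 4 weekly + 6 + 8 twice-monthly = 26 per person.
- All draws: 6 x 22 + 12 x 22 + 24 x 26 = 132 + 264 + 624 = 1,020.
- Draws in treatment windows of treated arms: 12 x 8 + 24 x 14 = 96 + 336 = 432.
- Share: 432/1,020 = 42%. By arm it is 8/22 = 36% in arm 2 and 14/26 = 54% in arms 3 and 4.

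Sensitivity: with re-treatment at week 4, arms 3 and 4 have 8 + 0 + 6 + 10 = 24 draws each, the total is 132 + 264 + 576 = 972, and the share is 432/972 = 44%. With week 12 the count is 8 + 6 + 6 + 6 = 26 and the share stays at 42%. The protocol does not state whether the DT0 and DRT0 samples are taken before or after the dose. If all are taken before it, those 36 + 24 = 60 draws cannot coincide with a reaction to that dose, and the share at week 8 falls to 372/1,020 = 36%.

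**What one unrecorded event does.** The event is assumed; the protocol gives no rate. In an arm of 12, one missing grade 3 event turns 1/12 = 8.3% (exact 95% CI 0.2 to 38.5%) into 0/12 (0 to 26.5%). With 8 evaluable it turns 1/8 = 12.5% (0.3 to 52.7%) into 0/8 (0 to 36.9%).

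**The case against.** The case against is substantial. Leaving trivial, expected puncture effects off the AE form is a reasonable choice in a 42-person descriptive pilot. The exemption covers only symptoms associated with venepuncture, so a drug reaction is lost only if it is misattributed. The same section goes on to name graver complications (arterial or nerve injury, vessel occlusion) without exempting them, which suggests that minor effects were meant. SAEs and grade 4 events remain reportable. No passage names pre-syncope as a reaction to either drug, and section 7.1.1 calls the ivermectin risk below the threshold almost negligible. All of this stands and limits the point. It does not remove the mismatch between sections 7.1.2, 4.3.2 and 7.2, because an implied grade limit is not a stated one.

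A reader might infer more than the protocol supports:

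- That every pre-syncope at a draw visit goes unrecorded. Only those attributed to the needle do.
- That the omission falls mainly on days when drug reactions are sought. Fewer than half of the scheduled draws fall in treatment windows of treated arms.
- That both safety endpoints are biased downward. A true needle reaction would not normally enter the grade 1-2 endpoint, which requires at least a possible relation to therapy; only misattribution affects it.
- That an assumed pre-syncope rate per draw, multiplied by 1,020 draws, gives the number of lost drug reactions. It would give needle-associated episodes, including those at 132 draws in untreated controls.
- That no trace is left. The text bars documentation as an AE, not source notes, and section 7.7 places an independent safety monitor on site.

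**Conclusion.** The concern holds as a minor inconsistency. Section 7.1.2 exempts pre-syncope without a grade limit, while sections 4.3.2 and 7.2 count such events whatever their cause. The attribution is made before recording, by an unblinded investigator, and the exemption applies equally at DT0, DT+1, DRT0 and DRT+1. Its reach is non-serious grade 1-3 events attributed to the draw.

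The 42% share of draws in treatment windows describes opportunity for overlap, not loss. It rests on week-8 re-treatment and 14-day visit spacing. How many drug reactions would go missing cannot be estimated from the protocol, and the number may be zero. No sample size or efficacy figure is affected.

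**What to change.** In section 7.1.2, limit the exemption to minor bruising and local tenderness at the puncture site, and state that SAE reporting is unaffected by it. Record pre-syncope as an AE with its grade, its onset relative to dose and to draw, and its relatedness. Report venepuncture-attributed events on a separate line, so that they can be told apart from possible drug effects, and count those of grade 3 in the primary safety endpoint as section 4.3.2 already provides.

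An explicit grade ceiling on the exemption would also remove the direct conflict with section 4.3.2. It would still leave the attribution of lower-grade episodes outside section 7.5.

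The cost is a one-sentence amendment and a few extra entries at visits that already record AEs. The downside is slightly higher AE counts in all arms, controls included, most of them probably true needle reactions.
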